**2.10 Will blood samples be obtained as part of this research study?**

No

**2.11 What is the total duration of the subject's participation in this research study across all visits, including follow-up surveillance?**

The minimum follow-up will be 12 months. However, depending on the time of the enrollment, patients enrolled at the beginning of the study will be followed up for up to 48 months maximum.

**2.12 Does this research study involve any type of planned deception?**

No

**2.13 Does this research study involve the use of UPMC/Pitt protected health information that will be de-identified by an IRB approved "honest broker" system?**

No

**2.14 Will protected health information from a UPMC/Pitt HIPAA covered entity be accessed for research purposes or will research data be placed in the UPMC/Pitt medical record?**

Yes.

If you answer Yes, you are required to submit this study to the Center for Assistance in Research using e-Record (CARE). Per UPMC Policy HS-RS0005, all research projects that access or involve UPMC electronic protected health information (e-PHI) must be submitted to CARE, with the exception of clinical trials that are contracted through the UPMC Office of Sponsored Programs and Research Support (OSPARS). Complete the online submission form at <http://www.eresearch.pitt.edu/request.aspx>. After the study is submitted in OSIRIS, a CARE representative will conduct a review. You will be notified once your CARE review is complete or if anything further is needed. For additional information, please see <http://www.eresearch.pitt.edu/>.

**Describe the medical record information that will be collected from the UPMC/Pitt HIPAA covered entity and/or the research-derived information that will be placed in the medical records.**

We inform the clinical team taking care of the patient in hospital of the results of their PHQ-2/PHQ-9 depression screen in a brief note placed on the patient's chart that will encourage the team to follow-up with the patient on this finding, if necessary. Our study nurses will also abstract portions of the medical record on all patients who meet inpatient protocol-eligibility to continue in our trial and consent to enroll prior to hospital discharge (e.g., medications, medical diagnoses, lab results). However, we will only collect information on tests that have been ordered as part of routine care and will never request any tests be ordered for research purposes. Our blinded telephone assessors will routinely ask study patients about any hospitalizations, cardiac events, or mental health visits they may have experienced since their last assessment at UPMC and non-UPMC facilities. As in our R34 pilot study (IRB 0701041), we will request the UPMC e-Record team to send us an automatically-generated hospital discharge summary anytime a study patient is discharged from one of the 13 UPMC acute care hospitals located across western Pennsylvania over the duration of their study participation. Our physician-led “Key Events Classification Committee” will then classify the event cause using a detailed protocol we developed. At the end of the Intervention Phase of our Trial, we will obtain claims data from UPMC Health plan. Specifically, we will request information on the type of service, service dates, amount paid to the provider, beneficiary copayment, and primary and secondary ICD-9 and CPT4 codes for each episode of care over the course of their enrollment so we may conduct our Project's economic analyses (C14c).

**2.14.1 Will protected health information from a non-UPMC/Pitt HIPAA covered entity be obtained for research purposes or will research data be placed in the non-UPMC/Pitt medical record?**

Yes

**If Yes, describe how the HIPAA requirements will be met:**

As described in 2.14, our blinded telephone assessors will routinely ask study patients about any hospitalizations, cardiac events, or mental health visits they may have experienced since their last assessment at UPMC and non-UPMC facilities. Whenever a death, hospitalization, or other cardiac or potentially life-threatening event is discovered, we will obtain the relevant medical records also from non-UPMC facilities, so that our physician-led “Key Events Classification Committee” can classify the event cause using a detailed protocol we developed.

At the end of the Intervention Phase of our Trial, we will obtain claims data from Medicare (via the Research Data Assistance Center (ResDAC); <http://www.resdac.org/AboutUs/Index.asp>), and Highmark Blue Cross/Blue Shield. Specifically, we will request from subjects’ insurers information on the type of service, service dates, amount paid to the provider, beneficiary copayment, and primary and secondary ICD-9 and CPT4 codes for each episode of care over the course of their enrollment so we may conduct our Project’s economic analyses (C14c).

**I, [name], certify that any member of my research team accessing, reviewing and/or recording information from medical records have completed HIPAA Researchers Privacy Requirements (Formerly RPF Module 6) training. The HIPAA certificates must be available for review if audited but do not need to be uploaded into this OSIRIS application.**

Yes

**2.14.2 Are you requesting a waiver of the requirement to obtain written HIPAA authorization for the collection of the PHI from a UPMC/Pitt covered entity? Note that the University of Pittsburgh IRB cannot grant a HIPAA waiver for entities outside of UPMC/Pitt.**

No

**2.15 Does this research study involve the long-term storage (banking) of biological specimens?**

No

**2.16 Will research participants be asked to provide information about their family members or acquaintances?**

Yes

**2.16.1 Describe what information about the third party will be obtained from the participant:**

We will ask for secondary contact information (spouse, adult child, friend) so that we may contact patients in the event we are unable to reach the patient at a later date (e.g., 2-week follow-up). We will not ask for any other information about any third party.

**2.16.2 If the information about the third party is of a private nature, can the identity of the third party be readily ascertained or associated with this information?**

Yes.

**Describe the private information that will be collected and recorded about the third party:**

Name, phone number, relationship to study patient.

**2.17 What are the main outcome variables that will be evaluated in this study?**

HRQoL is increasingly recognized as an important outcome, particularly for disorders causing disabling daily symptoms. We selected the generic and widely used SF-36 Mental Component Summary (MCS) as our primary outcome measure of HRQoL as: (1) we and others have demonstrated its sensitivity to changes in mood; (2) it has been validated for use in patients with HF; and (3) it allows us to measure the impact of our “blended” intervention on two conditions simultaneously. Since a more disease-specific quality of life measure can sometimes provide a more sensitive indicator of program benefit, we also selected the Kansas City Cardiomyopathy Questionnaire (KCCQ) and the version of the Hamilton Rating Scale for Depression (HRS-D).

**2.18 Describe the statistical approaches that will be used to analyze the study data.**

We will evaluate the comparative effectiveness of our interventions to address our co-primary hypotheses on HRQoL and a broad variety of other outcomes of interest (e.g., HRS-D) using ITT mixed-effects repeated measures models with time (random) gender, treatment, and interaction terms. We will also evaluate time to first hospitalization, death, and composite major adverse cardiac event (all-cause death, MI, stroke, and rehospitalization for cardiac cause) using Kaplan-Meier survival analyses with non-directional 2-tailed log-rank tests to evaluate differences by study arm. We will apply similar techniques to describe and compare subjects in our non-depressed cohort to depressed randomized study subjects. We will first examine our data by study arm in univariate fashion using cross tabulations, histograms, and box plots applying standard statistical tests to assess covariate balance by randomization status and recruitment site, and adjusting for baseline differences in our multivariable models where appropriate. To handle missing data, we will first investigate the missingness process and investigate the reasons for dropouts, and use a likelihood-based or multiple imputation-based procedure if “missing at random” (MAR) is confirmed or consider selection models with a logistic dropout process or other model as found appropriate if the missingness (dropout) is nonignorable (missing not at random (MNAR)).

**2.19 Will this research be conducted in a foreign country or at a site (e.g., Navajo Nation) where the cultural background of the subject population differs substantially from that of Pittsburgh and its surrounding communities?**

No

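### Kaplan–Meier for time to first hospitalization, with deaths censored, overstates the actual probability of admission; a cumulative incidence curve with death as a competing event should replace it

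*Protocol*

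**What the plan says.** Protocol section 2.18 lists three time-to-event outcomes and gives all three the same method: "time to first hospitalization, death, and composite major adverse cardiac event (all-cause death, MI, stroke, and rehospitalization for cardiac cause) using Kaplan-Meier survival analyses". The arms are compared "with non-directional 2-tailed log-rank tests to evaluate differences by study arm". The section does not say how a death before any admission is coded, and it names no competing-risk method.

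Section 2.11 sets a minimum follow-up of 12 months and adds that "patients enrolled at the beginning of the study will be followed up for up to 48 months maximum". Section 3.13 requires systolic heart failure with an ejection fraction of at most 40% and NYHA class II, III or IV symptoms. Sections 2.14 and 2.14.1 provide for collecting hospitalizations and deaths and for classifying their cause by committee.

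First hospitalization is not primary. Section 2.17 names the SF-36 MCS "as our primary outcome measure of HRQoL".

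**The concern.** Death and first hospitalization compete: once a patient has died, a first admission is impossible. Kaplan–Meier has only two states for a patient who leaves the risk set, event or censored. Coding the death as an event would turn the outcome into death or hospitalization, which is not what is listed. That leaves censoring, which treats the dead patient as someone who could still be admitted later. The curve then describes admission in a setting where deaths do not occur, and only if death and admission are independent. It does not describe the share of patients who are in fact admitted.

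The share admitted is what most readers will take from the curve. Section 1.2 lists cardiovascular events, utilization and costs among the secondary hypotheses, and section 1.4 presents fewer readmissions as a reason why heart failure programs are being deployed. An admission probability that is too high, by an amount that grows with follow-up and with mortality, would carry into those readings.

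**Working it through.** **Which outcomes are affected**

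| Outcome in 2.18 | Can death prevent it? | Kaplan–Meier as absolute risk |
|---|---|---|
| Death | No, it is the event | Appropriate |
| Composite | No, all-cause death is a component | Appropriate |
| First hospitalization | Yes | Overstates if deaths are censored |

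**Inputs**

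- From the protocol: evaluation times of 1 and 4 years, the minimum and maximum follow-up in section 2.11.
- Not in the protocol: admission and death rates for the trial. There is therefore no stated figure to reproduce, and all rates below are assumptions.
- Assumed constant hazards: first admission *h* = 0.5 to 1.2 per year; death before admission *d* = 0.05 to 0.15 per year.

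**Formulas**

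- With deaths censored: 1−KM(t) = 1 − exp(−*h*t).
- Actual probability of admission by time t (cumulative incidence): CIF(t) = *h*/(*h*+*d*) × [1 − exp(−(*h*+*d*)t)].

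**One case in full** (*h* = 0.8, *d* = 0.10)

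- 1 year: 1−KM = 1 − exp(−0.8) = 0.551; CIF = (0.8/0.9) × [1 − exp(−0.9)] = 0.527; excess 2.3 points before rounding.
- 4 years: 1−KM = 1 − exp(−3.2) = 0.959; CIF = (0.8/0.9) × [1 − exp(−3.6)] = 0.865; excess 9.5 points before rounding.

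**Corners of the assumed range**

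| *h* | *d* | 1−KM, 1 yr | CIF, 1 yr | Excess (points) | 1−KM, 4 yr | CIF, 4 yr | Excess (points) |
|---|---|---|---|---|---|---|---|
| 0.5 | 0.05 | 0.393 | 0.385 | 0.9 | 0.865 | 0.808 | 5.6 |
| 0.5 | 0.15 | 0.393 | 0.368 | 2.6 | 0.865 | 0.712 | 15.3 |
| 1.2 | 0.05 | 0.699 | 0.685 | 1.4 | 0.992 | 0.953 | 3.8 |
| 1.2 | 0.15 | 0.699 | 0.659 | 4.0 | 0.992 | 0.885 | 10.7 |

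The excess is about 1–4 points at 12 months and 4–15 points at 48 months.

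**Wider assumptions**

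The only mortality figure in the protocol is national (section 1.3): 280,000 deaths among 6.6 million patients, a crude 4.2% per year. Take annual death before admission from 4.2% to an assumed 25%, and 12-month 1−KM from 40% to 60%. The excess is then about 1–7 points at 12 months and 4–26 points at 48 months.

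**What this does to a comparison of arms**

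Suppose both arms have the same admission hazard, *h* = −ln(0.5) = 0.693. Annual death is 20% in one arm (*d* = −ln(0.8) = 0.223), and the death hazard ratio is 0.7 in the other (*d* = 0.7 × 0.223 = 0.156).

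- Kaplan–Meier: identical curves, 93.8% at 48 months in both arms.
- Cumulative incidence at 48 months: 73.7% in the higher-mortality arm, 78.9% in the lower. At 12 months: 45.4% and 46.7%.
- Death or first admission at 12 months, 1 − exp(−(*h*+*d*)): 1 − exp(−0.916) = 60.0% and 1 − exp(−0.849) = 57.2%.

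The log-rank test compares admission hazards among patients alive and not yet admitted. It correctly sees no difference here. What the Kaplan–Meier curves miss is that the proportions actually admitted differ. Cumulative incidence shows this, but on its own it makes the arm with more deaths look better; death or first admission restores the order.

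**The case against.** The strongest defence is that the planned comparison is sound. With deaths censored, the log-rank test validly compares cause-specific hazards, and section 2.18 attaches Kaplan–Meier to that test without saying that 1−KM will be reported as an absolute risk. The outcome is not primary, the 12-month excess is only a few points under the assumed hazards, and 48 months is reached only by the earliest enrolled. All of this stands, and it confines the fault to the curve. It does not remove the fault: a Kaplan–Meier curve of first hospitalization will be read as a probability of admission.

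Two stronger readings are tempting, and the protocol supports neither.

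- A reader might infer that deaths are treated as dropout in the MCS analysis, so that the model supplies quality-of-life values after death. Section 2.18 does not say so. It states that "we will first investigate the missingness process and investigate the reasons for dropouts". It provides likelihood or multiple imputation under missing at random, and otherwise would "consider selection models with a logistic dropout process or other model as found appropriate if the missingness (dropout) is nonignorable". Deaths are identified separately, so they can be told apart from dropout. How death enters a quality-of-life analysis is commonly settled in a statistical analysis plan, which is not at hand.
- A reader might infer that a harmful mortality difference could be hidden. Death has its own Kaplan–Meier and log-rank analysis and is part of the composite. If anything the direction is the reverse: overstating admission more in the arm with more deaths makes that arm look worse.

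**Conclusion.** The point holds for one non-primary outcome and one use of it: the Kaplan–Meier curve for first hospitalization, read as the probability of being admitted. If deaths are censored, that probability is overstated by about 1–4 percentage points at 12 months and 4–15 at 48 months. The size rests on assumed constant hazards, because the protocol gives no trial rates; the direction does not depend on them. The hospitalization log-rank test, the analyses of death and the composite, and the co-primary MCS hypotheses are not called into question.

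**What to change.** In section 2.18, treat first hospitalization separately from the other two outcomes:

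1. Replace its Kaplan–Meier curve with the Aalen–Johansen cumulative incidence by arm, with death before admission as a competing event.
2. Keep the two-tailed log-rank test, and label it as a test of the cause-specific hazard of hospitalization.
3. Add time to death or first hospitalization, so that cumulative incidence is not read without mortality. The planned composite does not serve this purpose, because it counts only rehospitalizations for cardiac cause.
4. Leave Kaplan–Meier in place for death and for the composite.

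The cost is a few sentences, standard software and one added analysis. No new data are needed, since deaths and hospitalizations are already to be collected and classified.

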### **1.2 Specific Aims: List the goals of the proposed study.**

Specific Aims are to: (1) evaluate the effectiveness of a telephone-delivered “blended” collaborative care intervention for treating both depression and HF that could be readily adopted into routine clinical practice if proven effective; and (2) advance our understanding of the moderators and mediators of depression treatment on clinical outcomes.

We propose to screen hospitalized adults with HF for depression and then randomize 625 protocol-eligible patients with a cardiac ejection fraction (EF)  $\leq 40\%$ , New York Heart Association (NYHA) class II-IV symptoms, and who have at least a moderately elevated level of depressive symptoms (PHQ-9  $\geq 10$ ) at two-weeks following hospital discharge to a 12-month course of either: (1) Collaborative care for treating both HF and depression (“blended”); (2) Collaborative care for treating HF alone (enhanced usual care (eUC)); or (3) Their doctors’ “usual care” for treating HF and depression (UC).

Additionally, we will enroll 125 non-depressed HF patients to better evaluate the benefits derived from treating depression and, together with UC, control for any secular changes in the management of HF as elements of the 2010 Affordable Care Act are phased-in (Total N=750). Our co-primary hypotheses will test whether “blended” collaborative care can produce at 12-months follow-up a: (A) moderate 0.50 effect size (ES) or greater improvement in HRQoL vs. UC; and (B) clinically meaningful 0.30 ES or greater improvement in HRQoL vs. eUC. Our secondary hypotheses will evaluate in comparisons with eUC and UC the effects of our “blended” intervention on mood, functional status, delivery of and adherence with guideline-consistent care, incidence of cardiovascular events, health care utilization, and costs.

Though not explicit objectives of this application, the proposed trial will also serve as the basis for ancillary studies to examine the genomic moderation of treatment effects and such mediating mechanisms as blood pressure control, sleep quality, and chronic inflammation to further advance our understanding of how depression and its treatment affects clinical outcomes.

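### Section 2.18 makes the missing-data method for the co-primary HRQoL analyses depend on confirming MAR, which observed data cannot do, and otherwise offers an open list of models

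*Protocol*

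**What the plan says.** The co-primary hypotheses in protocol section 1.2 "test whether “blended” collaborative care can produce at 12-months follow-up" a 0.50 effect size against UC and a 0.30 effect size against eUC. Section 2.17 names the "SF-36 Mental Component Summary (MCS) as our primary outcome measure of HRQoL".

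Section 2.18 names the model for these hypotheses: "ITT mixed-effects repeated measures models with time (random) gender, treatment, and interaction terms". It then sets out how missing data will be handled. As a first step, "we will first investigate the missingness process and investigate the reasons for dropouts". What follows depends on the result: a likelihood-based or a multiple-imputation procedure in one case, a different approach in the other. The turning point reads "MAR) is confirmed or consider selection models with a logistic dropout process or other model as found appropriate if the missingness (dropout) is nonignorable". The section gives no criterion for deciding which case applies.

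**The concern.** The choice between the two branches rests on a question that data cannot answer. MAR and MNAR make different statements about values that were never observed, so examining the observed values cannot establish either one.

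A rule whose condition cannot be met still has to be applied by someone, and in practice that means judgement. Here the judgement is exercised after the missingness has been examined, and the second branch ends in whatever model then seems suitable. The co-primary HRQoL analysis is named in one sentence and made replaceable a few sentences later.

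At stake is whether the main result comes from an analysis fixed in advance. Selection models make this sharper. They identify the treatment effect through distributional assumptions that the data cannot check, so the answer may turn on which model was picked.

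**Working it through.** **Inputs from the protocol.** Effect sizes are 0.50 (Blended against UC) and 0.30 (Blended against eUC), from section 1.2. Arm sizes are 250 Blended, 250 eUC and 125 UC, from section 3.11; 250 + 250 + 125 = 625, which agrees with section 1.2. The protocol gives no dropout rate, and section 3.12 refers the sample-size justification to the grant application. There is therefore no plan figure on missing data to reproduce.

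**Step 1: what observed data can and cannot show.** Write the 12-month mean in one arm as

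arm mean = (1 − m) × observed mean + m × (mean predicted under MAR + delta),

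where m is the share missing and delta is how far the missing outcomes depart from the MAR prediction. The data supply m, the observed mean and the MAR prediction. They say nothing about delta: every value gives the same observed-data likelihood. MAR is the case delta = 0, and no inspection of the data can select it. What can be tested is whether missingness is related to baseline or earlier scores. Such a relation rejects missing completely at random, but it is compatible with both MAR and MNAR. Recorded reasons for dropout bear on which is more plausible and confirm neither.

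**Step 2: apply the rule as written.**
- Branch 1 requires MAR to be established. By step 1 this cannot happen.
- Branch 2 requires the missingness to be nonignorable. By step 1 this cannot be established either.
- Read literally, neither branch is ever triggered. Read loosely, the analyst decides without a criterion.
- Branch 1 allows two methods. Branch 2 only asks that selection models be considered, and then admits any other model judged suitable.

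**Step 3: scale, on assumed values.** Suppose the departure is confined to the Blended arm, where missing outcomes are delta SD worse than MAR predicts. An MAR estimate is then too favourable by m × delta. If that estimate is 0.30 against eUC, the effect is 0.30 − m × delta. All m and delta values are assumptions.

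| m | delta (SD) | shift = m × delta (SD) | effect against eUC (SD) |
|---|---|---|---|
| 10% | 0.25 | 0.025 | 0.275 |
| 10% | 0.50 | 0.05 | 0.25 |
| 20% | 0.25 | 0.05 | 0.25 |
| 20% | 0.50 | 0.10 | 0.20 |
| 30% | 0.25 | 0.075 | 0.225 |
| 30% | 0.50 | 0.15 | 0.15 |

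The effect reaches zero at delta = 0.30 / m, that is 3.0, 1.5 and 1.0 SD for m = 10%, 20% and 30%. If both arms had the same m and the same delta, the shift would be m × delta − m × delta = 0.

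**The case against.** The strongest reply is that a primary analysis already exists. Section 2.18 names the intention-to-treat mixed model first. Fitted by likelihood in the usual way, that model is valid under MAR, and the alternative is only to be considered. This stands as mitigation: the choice is not wholly free, and the repair is short. It does not remove the defect, because the conditional clause still permits the named model to be replaced and says nothing definite about when or by what.

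A second reply is that the statistical analysis plan may settle the matter. That would answer a complaint about missing detail. Here the protocol states a rule. A plan that follows it inherits a condition that cannot be met, and a plan that drops it departs from the protocol.

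A third reply concerns the size. The shifts above are the bias of any MAR analysis under a one-arm MNAR departure. The primary analysis recommended here would carry the same bias. The departure is also placed in one arm only, and the 0.15 SD figure is the extreme corner of the assumed range. All of this is correct. The figures serve only to show that a sensitivity analysis is worth having. They do not measure what the switch costs, and no inflation of the false-positive rate has been calculated.

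**Conclusion.** The point holds. Section 2.18 makes the missing-data method conditional on something that observed data cannot establish, and it opens the co-primary HRQoL analysis to a data-driven replacement from an unbounded list. This follows from the definitions of MAR and MNAR and from the wording, and needs no numerical assumption. The 0.025-0.15 SD range rests wholly on the assumed 10-30% missing and 0.25-0.50 SD departure in the Blended arm alone.

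A reader might infer two stronger claims that the protocol does not support.

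- **That deaths are handled as ordinary dropout.** No section says so. Section 2.18 treats death as an outcome in its own right: "We will also evaluate time to first hospitalization, death, and composite major adverse cardiac event (all-cause death, MI, stroke, and rehospitalization for cardiac cause". The second part of section 2.14.1 provides for obtaining records and classifying the cause "Whenever a death, hospitalization, or other cardiac or potentially life-threatening event is discovered". The protocol is silent on how the MCS after death enters the model. That detail is commonly left to the statistical analysis plan, so the silence is not counted here.
- **That the model is chosen after unblinding.** Section 2.18 does not say when the missingness will be examined or whether treatment arm will be visible. The one look by arm that it describes is for covariate balance.

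**What to change.** In section 2.18:

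1. Delete the condition that MAR be confirmed, and the branch that depends on it.
2. State that the intention-to-treat, likelihood-based mixed-effects repeated measures model, under an assumed MAR, is the primary analysis for both co-primary hypotheses whatever the missingness looks like.
3. Replace the switch with a prespecified MNAR sensitivity analysis that is always reported. One suitable choice is delta-adjusted multiple imputation by arm, with delta increased until the conclusion changes, so that readers can judge whether that value is plausible.
4. Keep the review of missingness and of reasons for dropout as description that helps interpret the sensitivity analysis, with no role in choosing the primary model.

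The cost is a few sentences and a little more analysis work. No new data are needed, and the named primary model does not change.
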